One of every 500 African Americans has SCD, and one of every 12 African Americans has SCT [1]. SCT is usually asymptomatic but, as an autosomal recessive condition, persons with SCT are at risk for having children with SCD if their reproductive partners have SCT or SCD. A rough estimation based on prevalence of SCT and SCD shows that if no action is taken, 0.94 in 500 births among African Americans will exhibit SCD, very close to the reported statistic of 1 in 500 births. Thus, these rates suggest that the *at-risk* population is not currently engaged in systematic efforts to reduce the risk of their children inheriting SCD, an important scientific premise for the proposed study. If both reproductive partners have SCD, for each pregnancy, there is 100% chance of the child having SCD. If one partner has SCD and one has SCT or another hemoglobinopathy, for each pregnancy, there is 50% chance of the child having SCD. If both partners have SCT, for each pregnancy, there is 25% chance of the child having SCD. If only one partner has SCD or SCT and the other partner has normal hemoglobin (Hb A), for each pregnancy, there is 0% chance the child will have SCD. Examples of two behaviors needed for a person with SCD or SCT to reduce the risk of having a child with SCD include [1] talking with one’s potential reproductive partner about sickle cell status and [2] seeking partners with Hb A. These behaviors, however, are not well-known or easy to accomplish for them or for any of the other 3 million Americans with one of the 10,000 other single-gene diseases (e.g., Huntington disease, Fragile X syndrome, cystic fibrosis, or muscular dystrophy) [13]. Study findings will provide evidence on how to mitigate uninformed inheritance of SCD worldwide and serve as an intervention model in follow-up to genetic counseling for other single-gene disorders.

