In a series of four studies [14–17] we systematically established that the control and experimental interventions were relevant to the SCD community and that the participants were sufficiently engaged with the online computer delivery system. The CHOICES intervention significantly increased knowledge for young adults with SCD or SCT and this difference was sustained 24 months later. Intentions and behaviors were not significantly different between groups, most likely because half of the recruited group was not *at risk* for their children inheriting SCD. We concluded, therefore, that the proposed RCT should focus on individuals *at-risk* for having a child with SCD and whose parenting plan indicate that they want to avoid having a child with SCD and plan to have a child within the study period.

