### Eligibility criteria

Participants are eligible to participate in the CHOICES study if they meet the following eligibility criteria: Confirmed diagnosis of SCD, SCT, or another hemoglobinopathy, able and intends to conceive a child, wants to avoid the risk of having a child with SCD, are able to speak and read English, are at risk for having a child with SCD, and are between the ages of 18–45 years.

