#### Behavior: *At-risk* time

The *Behavior Questionnaire* is an 30-item, sex/gender-specific measure of reproductive health behavior relevant to people with SCD or SCT [20, 21]. The items are part of the SCKnowIQ and focus on behaviors and outcomes during the past 6 months relevant to the success of their parenting plan: a) partner’s sickle cell status; b) use of contraceptive methods; c) use of advanced reproductive technologies such as in vitro fertilization (IVF); d) pregnancy; e) use and outcome of prenatal testing; f) pregnancy outcome (e.g., pregnancy-induced changes, abortion, miscarriage, birth of an infant with SCD, birth of an infant unaffected by SCD or SCT, birth of an infant who is a carrier of SCT). The *at-risk* time of each participant during the 24-mo study will be obtained by aggregating the at-risk status outcomes of all visits. Based on their answers to the behavior questions (a-f) at each visit, we will assess whether they are at risk in the previous six months. A person is considered not at risk if their behaviors meet any of the following criteria: 1) their partner has Hgb A; 2) they always use effective birth control methods; 3) they use prenatal testing or advanced reproductive technology to ensure the baby is free of SCD (otherwise, a person will be considered *at risk*). The behavior items (f) will also allow us to calculate the number of children born during the study for descriptive purposes. The logical compatibility between behavior items and demographic items (SC status, number of children, etc.) in the same visit and across multiple visits of our previous studies and the participants’ responses to cognitive interviews in the preliminary study [16] attest to their validity. Since all participants will be at risk at baseline, the posttest *at-risk* score ranges from 0% of the time at risk to 100% of the time at risk across the 4 posttest measures after the baseline visit.

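### Entry requires being at risk without defining the term, while the endpoint defines it by behaviour, so the premise that everyone is at risk at baseline is not guaranteed

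*Protocol article*

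**What the plan says.** Under Eligibility criteria, entrants must meet this condition: "are at risk for having a child with SCD, and are between the ages of 18–45 years". The section does not say how being at risk is determined. The other criterion touching on behaviour is "able and intends to conceive a child, wants to avoid the risk of having a child with SCD". Nothing there concerns current contraception, prenatal testing or reproductive technology.

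The Introduction explains the risk through inheritance: "persons with SCT are at risk for having children with SCD if their reproductive partners have SCT or SCD". It also describes the target population as people who want to "avoid having a child with SCD and plan to have a child within the study period".

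The section Behavior: At-risk time gives the only operational rule. Status is judged at each visit for the preceding six months. A person counts as not at risk on meeting any one of three conditions: "1) their partner has Hgb A; 2) they always use effective birth control methods"; or "3) they use prenatal testing or advanced reproductive technology to ensure the baby is free of SCD". Everyone else is at risk. The section then introduces the range of the follow-up score with the clause "Since all participants will be at risk at baseline".

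**The concern.** One term does two jobs. At entry it is undefined, and the only explanation on offer is genetic. At the endpoint it is behavioural. The baseline premise is true only if both uses mean the same thing, and the article does not say that they do.

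This matters because at-risk status is the feature the trial was redesigned around. The Introduction attributes the earlier null result on behaviour, as the most likely cause, to half of that sample not being at risk. If some entrants already count as protected under the endpoint rule, the contrast in at-risk time may be diluted. If baseline status is taken to be the same for everyone, a covariate that is probably prognostic goes unused.

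**Working it through.** **Step 1: can an entrant score not at risk at baseline?** Take a participant with SCT whose partner has SCT, who has used effective contraception throughout the last six months and plans to conceive in the second year.

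| Test | Result |
|---|---|
| Confirmed SCT, aged 18–45, English-speaking | met |
| Able and intending to conceive | met; the criterion sets no date |
| Wants to avoid a child with SCD | met |
| At risk, read as in the Introduction | met; both partners have SCT |
| Child planned within the study period (Introduction) | met; follow-up is 24 months |
| Endpoint rule, previous six months | not at risk, because "2) they always use effective birth control methods" |

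This person can be enrolled and contradicts the premise.

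**Step 2: do the described procedures close the gap?** Before randomization, Screening and consent lists screening questions, consent, a telephone call and a record of the participant's own SCD or SCT status. Procedures has the software randomize after registration and then has participants complete baseline measures. The baseline Behavior Tool (Table 1) therefore cannot decide entry. The screening questions might, but they are not shown.

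**Step 3: reproduce the stated power.** Inputs from Sample power: at-risk time 30% ± 37% (CHOICES) and 41% ± 44% (e-Book), 430 participants, two-sided 0.05. I take 215 per arm; equal allocation is inferred from two groups and blocks of four.

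- Pooled SD = √((37² + 44²)/2) = √1652.5 = 40.65
- Standard error = 40.65 × √(2/215) = 3.92
- Power ≈ Φ(11/3.92 − 1.96) = 0.801 (noncentral t: 0.799)

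The stated 80% is confirmed. The knowledge endpoint (12.0 ± 3.0 against 11.1 ± 3.1) gives 0.864 against a stated 85%, and at-risk status does not enter that calculation.

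**Step 4: what dilution could look like.** Let f be the share of entrants already not at risk by the endpoint rule. The documents do not give f, so the values below are assumptions. Two further assumptions are needed: these entrants show no intervention effect, and the planning sample contained none of them. The difference is then 11 × (1 − f). Version A keeps the SD at 40.65. Version B puts the f share at 0% at-risk time in both arms, so each arm's variance is (1 − f)(s² + m²) − ((1 − f)m)², where m and s are that arm's planning mean and SD.

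| f (assumed) | Difference | Power, A | SD, B | Power, B |
|---|---|---|---|---|
| 0% | 11.0 | 80% | 40.65 | 80% |
| 10% | 9.9 | 71% | 40.04 | 73% |
| 20% | 8.8 | 61% | 39.10 | 65% |

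These rows show how sensitive power is under those assumptions. They do not estimate this trial's power.

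**The case against.** The strongest reply is that the article condenses a fuller protocol. The unseen screener may apply the endpoint rule, and the premise follows that rule in the same paragraph, so entry may well use it. That is possible, and one sentence saying so would settle the matter. But the premise is asserted in the text, and nothing shown supports it.

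Several stronger readings are tempting and should not be drawn:

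- *Eligibility is based on partner genotype.* The eligibility section leaves the term undefined. The genetic reading is a reasonable inference from the Introduction, not a stated rule.
- *Already-protected entrants have nothing to gain.* The endpoint covers 24 months. Someone who stops contraception to conceive with an SCT partner becomes at risk unless prenatal testing or reproductive technology is used. CHOICES presents those options and the e-Book does not, so the arms can diverge among these people.
- *Power is really 71% or 61%.* Those figures need an assumed f, a zero effect and an unstated fact about the planning sample. Sample power calls that sample at-risk without saying by which definition. If it was selected as this trial's sample will be, any dilution is already inside the 11-point difference.
- *The comparison is biased.* Randomization balances baseline status on average, and chance imbalance is covered by the type I error rate.
- *The premise discards the baseline value.* It only introduces the score range, and 0% to 100% over follow-up does not depend on it. Baseline behaviour is collected, and Aim 2 uses it.

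The choice of covariates may also sit in an analysis plan not shown. That is a fair answer to any complaint about omission, but not to the unsupported premise.

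**Conclusion.** The point holds as a mismatch of definitions. The stated criteria do not guarantee that all participants are at risk at baseline under the endpoint's own rule, and Step 1 gives a plain counterexample. It would fall away if the screener already applies that rule.

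No stated number is wrong. The effect is confined to the secondary endpoint and takes two forms: possible dilution, which cannot be sized from the documents, and lost precision if baseline status is treated as a constant. Knowledge, which decides the trial's success, is untouched. A reader might infer that the trial repeats its predecessor's fault. The documents do not support that, because at-risk status is now an entry requirement and even the genetic reading excludes people whose partner has normal haemoglobin.

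**What to change.** State in the eligibility criteria which definition of at risk applies at entry. If the six-month behavioural rule is already applied at screening, say so; the premise then stands and nothing else is needed.

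Otherwise, delete the clause claiming that all participants are at risk at baseline. Score baseline at-risk status by the endpoint rule from the Behavior Tool listed at baseline in Table 1, and include it as a covariate in the at-risk-time analysis. The tool is completed after randomization but before the intervention is delivered, so it is still a pre-intervention measure. The cost is wording and one model term, with no new data.

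Screening out current contraception users would also make the premise true, but it would turn away otherwise eligible volunteers whom CHOICES is meant to serve. That trade-off is debatable, and the point does not require it.

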#### Descriptive and exploratory variables

The *Demographic Questionnaire* includes items that are used to document the participant’s gender, age, ethnicity, marital status, years of education completed, annual family income, SCD of self/relative, SCT of self and partner, use of hydroxyurea, severity of SCD, type of insurance, number of previous pregnancies, number of children, prior use of computers, and current access to computers. These data are collected as composite demographic data for the purpose of assessing the representativeness of the participants and analysis of the baseline characteristics of a heterogeneous sample of mostly African Americans. Other details about the tool appear in Table 2. The Usability and Acceptability Instrument is a 20-item tool designed to evaluate participants’ perspective on the usability, acceptability and credibility of computer-based tools, such as CHOICES. The tool was validated in our preliminary studies as a method for identifying concerns about the study.

#### Statistical analysis

Data management and data analysis will be conducted by one of the MPIs and the study statistician, using statistical software R. All personnel with access to the data will be trained in the safety and security of privacy information during and after the study and will sign an oath of confidentiality prior to accessing any identifiable information. The data will be stored in a secure SQL database and will be exported to R for analysis. We will use an intention to treat approach, where all participants that are randomized will be included in our analysis.

Every effort will be taken in our software upgrade design to eliminate user errors; all data are entered directly by the participant using an interface tested with cognitive interview methods that informed the final interface design. Consistency checks will be built into the software so that inconsistent data (e.g., out of range or logically inconsistent with past data) will be flagged immediately and clarification from the users will be obtained. In addition, further and potentially more comprehensive consistency checks will be performed before data analysis. Inconsistent data points will be treated as missing and proper missing data processing (e.g., multiple imputation) will be applied. Based on our prior studies with this web-based software application, we expect the percentage of inconsistent data values to be very low (<0.5%).

For missing data, including those caused by participants missing visits, multiple imputation will be used to generate multiple completed datasets on which statistical inference will be performed and then aggregated. Missing at random assumption will be assessed and if necessary, sensitivity analysis will be performed using the pattern mixture model. Specifically, we will test various plausible selective missing mechanisms through post-processing of imputations to evaluate the robustness of our findings. We will consider a *p* value lower than 0.05 as statistically significant.

#### Aim 1

Multi-level regression analysis will be used to analyze the longitudinal data to estimate the effects of the CHOICES intervention on knowledge and behavior, where random effect terms will be used to accommodate the within-participant correlation between repeated measures collected over time from each participant. We hypothesize that the CHOICES group participants will have significantly higher knowledge scores and lower *at-risk* behaviors compared with e-Book group participants. The knowledge outcome is the primary endpoint for determining success of the RCT, with the at-risk behavior outcome as secondary.

#### Aim 2

We will compare the baseline knowledge and behavior by gender. We will also compare the intervention effects on different sexes by conducting regression analysis including gender, group assignment, and their interaction as predictors. Whereas this study is powered for detecting the intervention effects on the combined sample, not for determining difference between sexes, this valid subgroup analysis will provide important insight on potential difference in baseline characteristics and in intervention uptake by sex. We will also conduct exploratory analysis to investigate the relationship of SC status and other demographic characteristics such as age, education, among others and intervention acceptability with knowledge and behavior both at baseline and post-intervention. This exploratory analysis will provide insight on the baseline knowledge and behavior as well as intervention effects in different demographic groups and level of intervention acceptability, thus helping to identify groups most in need and most likely to benefit from the proposed intervention.

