### Specific aims

Building on findings from the preliminary studies, we now propose a fully-powered RCT with refined methods and intervention enhanced with nudges and tailored boosters to compare effects of e-Book and CHOICES interventions on genetic inheritance knowledge (knowledge) and reproductive health behaviors (behaviors) (Fig 1). Using referrals from clinics, community-based organizations, transit advertising, and social media to recruit an adequately powered sample, we will use web-based data collection (SCKnowIQ—baseline, posttest, 6, 12, 18, 24 months) and intervention delivery (Fig 2). We will use multi-level regression analysis to examine the intervention effect on knowledge and behaviors (time *at-risk*). We will also explore predictors of outcomes. In a sample of 430 young adults (18–45 years of age, with SCD or SCT), specific aims are to:

#### Aim 1

Compare e-Book and CHOICES groups for effects on (a) knowledge (primary endpoint), and (b) *at-risk* behaviors (secondary endpoint) measured with the SCKnowIQ, over time (baseline, posttest, 6, 12, 18, 24 months). We hypothesize that (a) across all time points post baseline, there will be higher knowledge scores, and (b) lower percentage time with *at risk* behaviors (*at-risk* time) in the CHOICES than in the e-Book groups.

#### Aim 2

Explore the relationship between the demographic factors (e.g., gender, SC status), acceptability, and the Aim 1 endpoints (knowledge, behavior). We will conduct subgroup analyses to provide insight into the baseline knowledge and behavior as well as the intervention effects in different demographic and acceptability groups.

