### Procedures

The RS will develop Facebook pages for the study recruitment and retention processes. We will provide the potential participants with a link to the study website where they complete screening questions. RS receives confirmation of eligibility and sets up a time to discuss consent. Participants are sent a link to sign an online consent form, and have questions answered by the RS, who directs them to provide verification of SCD or SCT status. Once the RS receives the verification and approves the participants for participation, RS registers participants and participants are prompted to create a login and password on the CHOICES website. The software application randomizes the participants based on registration information after verified by the RS. The participants complete baseline measures and receive the CHOICES or e-Book based on group assignment. Table 1 lists a summary of the study data collection and intervention points, including boosters at 6 and 12 months and nudges monthly during the first 12 months of the study. For all intervention sessions, the experimental group reads or listens to the CHOICES intervention and the control group reads or listens to the usual care materials (e-Book) on the computer or mobile devices. At each follow-up visit, participants enter data with the SCKnowIQ data collection app (Table 1). Participants receive payments after each verified task via their selected method (mail, digital).

**Table 1 pone.0294907.t001:** CHOICES sickle cell study data collection and intervention summary.

Study Event	Time Points (mo)					
	Baseline	Posttest	6	12	18	24
**SCKnowIQ** Computerized Questionnaires—Sickle Cell:						
**Knowledge** Questionnaire	X	X	X	X	X	X
**Behavior** Tool	X	X	X	X	X	X
Demographic Questionnaire	X					
Intervention Acceptability		X				X
**CHOICES**—**Intervention** X initial; O nudges and booster tailored to most recent responses	X		O	O		
**e-Book**—**Intervention** X initial	X					
**Computer Acceptability Scale**		X				X

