### Acceptability of interventions

At the conclusion of the preliminary study’s immediate posttest, participants in both groups were prompted by the computer to indicate what it was like to participate in the study and what they thought about the intervention program (Usability and Acceptability Instrument). Overall, they gave positive responses that included “great learning experience,” “great program,” “interesting,” “helpful,” and “informative.” Although a few of the participants in the e-Book group saw the content as a “refresher,” most participants in both groups found the content new and beneficial to their understanding and learning. Some of the participants went beyond focusing on their own learning and noted that the information would help stimulate awareness about SCD and SCT in individuals and communities. More of the CHOICES group than the e-Book group indicated that they “enjoyed” the learning and liked the various ways it was delivered including the presentation of the videos. Some participants clearly indicated that the computer was an easy, convenient, and “wonderful” way to convey this important information. As one participant said, “It beats classroom learning!” No negative comments were given about the use of computers. There were some suggestions about computer use, such as how to navigate the touch screen and desire to complete it at home on their own personal computers.

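### Aim 2 looks for intervention effects by level of acceptability, but acceptability is a rating of the assigned program taken after delivery, so those arm comparisons are not protected by randomization

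*Protocol article*

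**What the plan says.** Aim 2 under Specific aims announces "subgroup analyses to provide insight into the baseline knowledge and behavior as well as the intervention effects in different demographic and acceptability groups". The Aim 2 paragraph under Statistical analysis repeats this and adds a use for it: insight into "intervention effects in different demographic groups and level of intervention acceptability, thus helping to identify groups most in need and most likely to benefit". Acceptability is named there beside gender, SC status, age and education, with no distinction between them.

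The timing is in Procedures. The software randomizes first; then "The participants complete baseline measures and receive the CHOICES or e-Book based on group assignment". In Table 1 the row "Intervention Acceptability" is marked at posttest and at 24 months and is blank at baseline. The Computer Acceptability Scale row is marked the same way.

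On content, the section on acceptability of the interventions reports that in the preliminary study both groups were asked at posttest "what they thought about the intervention program (Usability and Acceptability Instrument"). It adds a difference by arm in the comments: "More of the CHOICES group than the e-Book group indicated that they" enjoyed the learning.

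Sample power calls the Aim 2 subgroup analysis exploratory and says the study is not powered for differences between acceptability groups.

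**The concern.** A subgroup comparison keeps the benefit of randomization when the subgroup is fixed before treatment starts. Acceptability is not. It is rated after the participant has seen either CHOICES (about 72 minutes on average in the preliminary work) or the e-Book (about 8.6 minutes). By 24 months only CHOICES participants will have had boosters and nudges. The two arms are rating different products.

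A participant who rates a short e-Book highly may differ in interest or engagement from one who rates a long multimedia program highly. If those traits also bear on knowledge or behavior, the arms differ within an acceptability level for reasons other than the intervention. The 24-month rating has a further weakness: it is taken at the same visit as the last outcome, so it cannot be assumed to precede that outcome.

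At stake is the targeting conclusion. A contrast of this kind could be offered as guidance on whom CHOICES helps most, although nobody's acceptability level is known until the program has been delivered.

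**Working it through.** **1. The plan's own figures, to fix the scale.** Sample power gives knowledge of 12.0 ± 3.0 against 11.1 ± 3.1 with 430 participants, taken as 215 per arm.
- Difference 0.9; SD = √((3.0² + 3.1²)/2) = 3.05.
- 0.9 / (3.05 × √(2/215)) = 3.06. Power = Φ(3.06 − 1.96) ≈ 86%, against the stated 85%. It reproduces.

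No figure is stated for Aim 2. The concern rests on design logic, and what follows is illustration only.

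**2. Order of events.** Randomization, then baseline measures, then the assigned program, then the first acceptability rating. No acceptability value exists before delivery.

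**3. Illustration A: acceptability shifted by arm, no true effect on knowledge.** All inputs are assumed, because the documents give no acceptability distribution by arm and no correlation.
- U is a standard normal trait such as engagement. Acceptability has unit variance within arm, correlates c with U, and is b SD higher in CHOICES. Knowledge has SD 3.05 and correlates k with U.
- The sample is split at the pooled median of acceptability. The split is a device for the illustration; the protocol does not specify one.
- Arm difference in knowledge within either half = 3.05 × c × k × φ(b/2) × [1/Φ(b/2) − 1/(1 − Φ(b/2))].

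| b | c | k | φ(b/2) × [...] | Arm difference, each half |
|---|---|---|---|---|
| 0.3 | 0.3 | 0.3 | −0.191 | −0.05 |
| 0.5 | 0.5 | 0.5 | −0.318 | −0.24 |
| 0.8 | 0.7 | 0.7 | −0.507 | −0.76 |

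The first and last rows are the corners of the assumed ranges. Simulation of the same model agrees to about 0.01 (one run put the ends at −0.06 and −0.75). The middle row is about a quarter of the 0.9-point planning effect (0.24/0.9 = 0.27).

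The difference is the same in both halves, so under these assumptions the contrast between high and low acceptability is not distorted.

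**4. Illustration B: the rating reflects the trait differently by arm.** Here the true effect is 0.9 for everyone, k = 0.5, there is no mean shift in acceptability, and the correlation of acceptability with U is 0.7 in CHOICES and 0.3 in e-Book.
- Mean of U in the high half is 0.798 × 0.7 in CHOICES and 0.798 × 0.3 in e-Book.
- Distortion = 3.05 × 0.5 × (0.7 − 0.3) × 0.798 = 0.49.
- Apparent effect: 0.9 + 0.49 = 1.39 in the high group and 0.9 − 0.49 = 0.41 in the low group.

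A uniform effect appears as effect modification.

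**5. When nothing goes wrong.** In this model the distortion is zero if acceptability or knowledge is unrelated to the trait (c = 0 or k = 0), or if the arm changes neither the level of acceptability nor its relation to the trait. The protocol gives no ground for assuming any of these.

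**The case against.** The planned analysis is less definite than the summary sentences suggest. The only effect-modification model that is spelled out is for gender, with an interaction with group. For acceptability, the first statement in each place is of a relationship with knowledge and behavior, which can be read as a plain association. The phrase about those most likely to benefit covers demographic groups too, for which it is legitimate. This narrows the point but does not remove it: both places still promise intervention effects by acceptability and draw the targeting inference from them.

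The evidence that the arm changes acceptability is thin. It is a qualitative account of comments, and the Abstract reports high acceptability of both programs. That stands, and it is one reason the size of any bias is unknown. The instrument is also described generally, as capturing a "perspective on the usability, acceptability and credibility of computer-based tools, such as CHOICES", but Table 1 and the Aim 2 paragraph both speak of acceptability of the intervention.

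Aim 2 is labelled exploratory and unpowered. That caveat concerns precision. Bias from conditioning on a post-randomization rating does not shrink with more participants, and the caveat does not qualify the targeting statement.

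A reader might go further and infer that the plan fixes a comparison of arms within acceptability strata, that its results will be biased by a known amount, or that a false signal of who benefits must follow. The documents support none of these. No split is specified, no input for the bias is given, and with a simple shift in acceptability both halves are biased equally. A false signal needs a further assumption, such as the unequal correlations in illustration B.

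**Conclusion.** The point holds as a matter of analysis choice. Aim 2 treats a rating of the assigned program, first taken after delivery, as if it were a baseline subgroup factor. Arm comparisons by that factor lack the protection of randomization and could mislead in either of the ways illustrated, and the rating cannot identify beneficiaries ahead of time.

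The size cannot be derived from the documents. The figures of about −0.05 to −0.76 points under no effect, and of about 1.4 against 0.4 under a uniform 0.9-point effect, depend wholly on assumed shifts and correlations. They show what is possible and do not predict a result.

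The reach is limited. The Aim 1 comparisons of knowledge and at-risk time are unaffected, and so are the Aim 2 analyses by gender, SC status, age and education. The change is worth making because it is easy and because the plan states the targeting inference outright.

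**What to change.** In both Aim 2 statements, limit effect-modification analyses and the statement about who is most likely to benefit to variables measured before the intervention: gender, SC status, age, education and baseline knowledge.

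Keep acceptability, but in a different role. Report it by arm at posttest and at 24 months, and describe its association with knowledge and behavior within each arm, saying that these associations are descriptive and not estimates of intervention effect. Note that the 24-month rating coincides with the last outcome.

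The cost is a change of wording in two places and the loss of one exploratory claim. Data collection, sample size, power and the Aim 1 analyses stay as they are.
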